## Abstract

**Background:**

Pain is common in men undergoing rigid cystoscopy. Even with the application of a lubricant containing 2 % lidocaine, about 76 % of men suffer from mild to severe pain when undergoing rigid cystoscopy. The most painful part of the procedure for men is when the cystoscope passes through the membranous urethra. Song et al. (Neurourol Urodyn 29:592–5, 2010) did autopsies on males and found that the dorsal nerve of the penis (DNP), the terminal branch of the pudendal nerve, innervates the membranous urethra in 53.3 % of specimens. In addition, the urethral mucosa has branches of innervated DNP. Dorsal penile nerve block (DPNB) is usually used for circumcision in children, and it has been shown to provide effective analgesia for penile surgeries. In this study, we hypothesized that DPNB could reduce the overall pain level in men during rigid cystoscopy.

**Methods/design:**

The trial is a prospective, randomized, double-blind, placebo-controlled, single-center trial to evaluate the effectiveness and safety of DPNB in analgesia for men undergoing rigid cystoscopy. Participants will be enrolled and randomly allocated into one of three groups according to the different analgesia regimens: 1) tetracaine gel group (DPNB with saline), 2) DPNB group (DPNB with ropivacaine plus plain lubricant), 3) combination group (DPNB with ropivacaine plus tetracaine gel). The primary outcome of this study is the visual analog scale (VAS, 0–10) for pain at cystoscopic inspection of the external sphincter. VAS scores evaluated at other time points serve as secondary outcomes. Vital signs are secondary outcomes that address the discomfort and pain during the procedure. Furthermore, the incidence of adverse events as secondary outcomes will also be recorded for evaluation of the safety of DPNB in rigid cystoscopy. Clinical assessments will be evaluated prior to DPNB, at administration of the lubricant gel, at cystoscopic inspection of the penile and bulbar urethra, external sphincter, prostate, and bladder, as well as at withdrawal of the cystoscope.

**Discussion:**

This research will determine the effectiveness and safety of DPNB in men undergoing rigid cystoscopy. The results of this trial may have important implications for exploring the role of DPNB in analgesia for cystoscopy in men.

**Trial registration:**

ClinicalTrials.gov identifier NCT02502487 (6 Jul 2015).

## Background

Cystoscopy is a kind of invasive manipulation often used by urologists for diagnosis and treatment of bladder cancer and other lower urinary tract diseases [1, 2]. Flexible cystoscopy cause less discomfort and pain than rigid cystoscopy, but it still cannot replace the rigid cystoscopy technique because of the latter’s lower cost and better optical area, and the fact that it is easy to orient [3].

Pain and discomfort is common in men undergoing rigid cystoscopy. Under general anesthesia, it was reported that 30 % of patients complain of “feeling unwell” within 1 week after rigid cystoscopy [4]. In outpatient settings, even with application of a lubricant containing 2 % lidocaine, about 76 % of men suffer from mild to severe pain when undergoing rigid cystoscopy, and approximately 27 % of patients could still feel mild to moderate pain 7 days after the procedure [5].

Since the urethra is longer and narrower in men, cystoscopy generally tends to be more painful for them [6]. The most painful part of the procedure for men is when the cystoscope passes through the membranous urethra [7]. Song et al. [8] performed autopsies on males and found that the dorsal nerve of the penis (DNP), the terminal branch of the pudendal nerve, innervates the membranous urethra in 53.3 % of specimens. In addition, the urethral mucosa is innervated by branches of DNP [9].

Currently, dorsal penile nerve block (DPNB) is usually used for circumcision in children, and it has been shown to provide effective analgesia for penile surgeries since it was first reported by Kirya and Werthmann in 1978 [10]. To date, whether DPNB could be applied in cystoscopy for analgesia has not been addressed. Since some men have DNP branches innervating the membranous urethra and urethra mucosa, we hypothesized that DPNB could overall reduce the pain level in men during rigid cystoscopy.

## Methods/design

### Trial design

The trial is a randomized, double-blind, placebo-controlled, single-center trial to evaluate the effectiveness and safety of DPNB for analgesia in men undergoing rigid cystoscopy. Participants will be randomized to one of three study groups according to different analgesia regimens: 1) tetracaine gel group (DPNB with saline), 2) DPNB group (DPNB with ropivacaine plus plain lubricant), 3) combination group (DPNB with ropivacaine plus tetracaine gel). The trial scheme is illustrated in Fig. 1.

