#### Tetracaine gel control group

For men in the tetracaine gel group, DPNB is performed with saline. Five minutes after DPNB, tetracaine gel is instilled, with a minimum dwell time of 3 min, before rigid cystoscopy.

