### Outcomes

#### Primary outcome

The primary outcome of this study is intensity of pain measured by a visual analog scale (VAS) at cystoscopic inspection of the external sphincter. VAS is an internationally recognized pain scale with 11 points, ranging from 0 (no pain) to 10 points (maximal pain). Pain can be rated as the following categories: no pain (0 points), mild pain (1–3 points), moderate pain (4–6 points), and severe pain (7–10 points). Participants will be well educated regarding the VAS once enrolled and asked to rate their pain level during the study.

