### Statistical analysis

Statistical analysis will be performed with the SPSS (version 18; SPSS Inc., Chicago, IL) and SAS (version 9.3; SAS Inst. Inc., Cary, NC). All statistical tests will be two-sided, and the level of significance will be set at 0.05. Data with a normal distribution will be expressed as mean ± SD and tested by one-way ANOVA with Dunnett’s post hoc test as appropriate. Continuous data without a normal distribution will be expressed as median with interquartile range and analyzed using the MIXED procedure of the SAS statistical program for repeated measures followed by Tukey-Kramer adjustments.

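### The hypothesis is about the block, but the plan sets no priority for combination vs tetracaine gel, the one comparison that isolates it; 56 per group gives 90 % power only for a single unadjusted two-group test

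*Protocol article*

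**What the plan says.** **Arms** (Protocol article, Trial design and Interventions). The first two are "1) tetracaine gel group (DPNB with saline), 2) DPNB group (DPNB with ropivacaine plus plain lubricant" and the third is "3) combination group (DPNB with ropivacaine plus tetracaine gel". The section on the tetracaine gel control group confirms the saline block: "For men in the tetracaine gel group, DPNB is performed with saline". No arm combines a saline block with plain lubricant. The Interventions headings call tetracaine gel the control and both ropivacaine arms experimental.

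**Hypothesis** (Background). "we hypothesized that DPNB could overall reduce the pain level in men during rigid cystoscopy". The abstract says the same.

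**Primary outcome.** "intensity of pain measured by a visual analog scale (VAS) at cystoscopic inspection of the external sphincter".

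**Sample size.** The plan gives 56 per group for a difference of 1.6 VAS units, with SD 2.6, α 0.05 and 90 % power. It does not say which two groups the 1.6 units separate.

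**Statistical analysis.** Tests are two-sided at 0.05. Normally distributed data are to be "tested by one-way ANOVA with Dunnett’s post hoc test as appropriate"; other continuous data go to a repeated-measures mixed model with Tukey-Kramer adjustment. The section names no reference arm, no primary contrast and no order of testing.

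**The concern.** The two comparisons with the control arm answer different questions. Combination vs tetracaine gel asks whether a ropivacaine block adds analgesia when the gel is held constant, which is a direct test of the hypothesis. DPNB alone vs tetracaine gel changes the block solution and the instilled product together, so it asks which of two regimens gives less pain.

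Two things are at stake. First, an effective block and an effective gel could cancel in the second comparison. With no contrast designated in advance, that null result could be taken as the trial's answer on the block. Second, the sample size is that of one comparison at the full 0.05, while the analysis section adjusts for several. The comparison that carries the hypothesis therefore has less power than the stated 90 %.

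**Working it through.** **1. What each comparison isolates.**

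| Comparison | Block | Instillation | Estimates, if effects add |
|---|---|---|---|
| Combination vs tetracaine gel | ropivacaine vs saline | same (tetracaine gel) | B |
| DPNB alone vs tetracaine gel | ropivacaine vs saline | glycerine vs tetracaine gel | B − G |
| Combination vs DPNB alone | same (ropivacaine) | tetracaine gel vs glycerine | G |

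B is the reduction in VAS due to the block and G the reduction due to the gel. The documents give no value for G.

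**2. The plan's own figure.** The inputs from the Sample size section are a difference of 1.6, SD 2.6, α 0.05 (two-sided, from Statistical analysis) and power 90 %.

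n = 2 × [2.6 × (1.960 + 1.282) / 1.6]² = 55.5, rounded up to 56 per group.

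The stated 56 is reproduced. It is the size for one two-group comparison with no multiplicity adjustment.

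**3. Power per comparison at 56 per group.**

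- SE of a difference = 2.6 × √(2/56) = 0.491.
- Standardised effect = 1.6 / 0.491 = 3.26.
- Residual df with three arms = 3 × 56 − 3 = 165.
- Single test at two-sided 0.05 (critical value 1.974): power 89.9 %.
- Dunnett, two comparisons with a shared control (critical value 2.23): power 84.6 %.
- Tukey, all three pairs: power about 81 %.

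Keeping 90 % per comparison under Dunnett would need about 65 per group: 2 × [2.6 × (2.212 + 1.282) / 1.6]² = 64.5, using the normal-approximation critical value 2.212.

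**4. How a working block can give a null DPNB-alone result.** Assume additivity and B = 1.6, and let G vary. The last three columns give the power at 56 per group to show DPNB alone better than gel. The fixed sequence tests combination vs gel first at 0.05 and DPNB alone vs gel second at 0.05 only if the first is significant.

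| G (assumed) | B − G | Unadjusted 0.05 | Dunnett | Fixed sequence |
|---|---|---|---|---|
| 0 | 1.6 | 90 % | 84.6 % | 83.1 % |
| 0.4 | 1.2 | 68 % | 58 % | 65 % |
| 0.8 | 0.8 | 37 % | 28 % | 36 % |
| 1.2 | 0.4 | 12 % | 8 % | 12 % |
| 1.6 | 0 | 2.5 % | 1.3 % | 2.5 % |

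Under the same assumptions, combination vs tetracaine gel estimates 1.6 whatever G is. Its power is about 90 % as the first test in the sequence and about 85 % under Dunnett.

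**5. What the fixed sequence changes.** It restores about 90 % for the isolating comparison. It also gives DPNB alone vs gel more power than Dunnett when G is 0.4 or more. If G = 0 it loses 84.6 − 83.1 = 1.5 points on that comparison.

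**The case against.** Much of the opposing case stands.

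- **Equal weight.** A reader might infer that the plan gives both comparisons equal weight. It does not say so. That reading rests on the absence of an order and on an adjustment that treats the comparisons alike. What the text supports is that no priority is set.
- **Whether DPNB alone vs gel can show anything about the block.** A reader might infer that it cannot. That is too strong. If DPNB alone were superior to an active gel, this would support the block, provided the gel does not itself worsen pain. Only a null or unfavourable result is ambiguous. The comparison is a legitimate double-dummy head-to-head, and it alone asks whether the block without anaesthetic gel does better than the gel.
- **Non-inferiority margin, placebo label and precision.** None of these is an error. The article makes no non-inferiority or equivalence claim. Saline block and glycerine are placebo components on an active background. The 95 % CI half-width of 1.974 × 0.491 = 0.97 VAS units is the same for every pair and is smaller than the 1.6 units the plan calls clinically relevant. A zero difference would thus exclude a 1.6-unit difference between those two regimens.
- **Detail left to another document.** The order of contrasts is often set in an analysis plan, and none is shown here, so its absence alone would be no finding. The article does, however, state both its sample-size basis and its multiple-comparison procedure, and these two do not match.
- **Choice of primary.** Combination vs gel measures the block on top of gel. Making it primary is one defensible choice; the sponsor may prefer to keep both comparisons co-equal, at the power that goes with that.

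**Conclusion.** The point holds in a limited form. The hypothesis is about the block, one comparison isolates it, and the plan gives that comparison no priority. The stated 90 % power applies to a single unadjusted test; under the stated Dunnett procedure it is about 85 % per comparison, a shortfall of about 5 points. A null or unfavourable result for DPNB alone vs tetracaine gel would be compatible with a fully effective block and should not be read as evidence against it.

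The identification of the isolating comparison follows from the arm definitions alone. The power figures rest on the plan's SD of 2.6, difference of 1.6 and 56 per group. The table over G also assumes additive effects and a block effect of 1.6; since the documents give no gel effect, it shows a range and not a prediction. The arithmetic behind 56 is correct for the single comparison it describes.

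**What to change.** Before unblinding, and dated as such because the trial is already recruiting:

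1. Name combination vs tetracaine gel as the primary contrast for VAS at the external sphincter, two-sided 0.05. State that the 1.6-unit difference, 56 per group and 90 % power refer to it.
2. Test DPNB alone vs tetracaine gel second, at two-sided 0.05, only if the first is significant. Report its estimate and 95 % CI in any case, interpreted as a comparison of two regimens. State that a null or unfavourable result does not show the block to be ineffective.
3. Treat combination vs DPNB alone as descriptive.

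For the primary outcome this sequence takes the place of Dunnett and controls the familywise error over both comparisons with the gel arm.

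**Cost.** A protocol and analysis amendment, with no added patients. DPNB alone vs gel becomes confirmatory only if the first test succeeds, and it loses about 1.5 points of power relative to Dunnett if the gel has no effect.

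**Alternative.** If the sponsor prefers to keep both comparisons co-equal under Dunnett, restate the power as about 85 % per comparison at 56 per group.

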**Fig. 1 Fig1:**
[figure not shown]
Trial scheme. DPNB, dorsal penile nerve block

### Ethics

This study was approved by the Clinical Trials and Biomedical Ethics Committee of West China Hospital of Sichuan University (Ref: 20150611) and was registered with the US National Institutes of Health Clinical Trials registry (NCT02502487). This trial will be performed according to the principles of the Declaration of Helsinki (Edinburgh 2000 version). Written informed consent will be obtained from each participant before enrollment.

### Randomization

A set of random numbers for the allocation sequence will be generated using a computerized SPSS software package (version 18; SPSS Inc., Chicago, IL, USA). Sealed, opaque assignment envelopes will be used for allocation concealment. The included participants will be randomly enrolled by sealed envelope and assigned to one of three groups (tetracaine gel, DPNB, or combination group) in a ratio of 1:1:1.

### Blinding

A nurse, who will open the sealed envelopes, will prepare the syringe containing either 0.3 ml/kg of 0.33 % ropivacaine (AstraZeneca Pharmaceutical, Inc., London, UK) or 0.3 ml/kg of saline for DPNB, and 10 ml of 1 % tetracaine gel (Xi’an Lijun Pharmaceutical Co., Ltd., Xi’an, China) or 10 ml of liquid glycerine (YunJia Medical Technology Co., Ltd., Harbin, China) for instillation. The participants, attending anesthesiologist and urologist, as well as the researchers will be not aware of the randomization. The allocation concealment will not be exposed until the final data analysis report is completed.

### Participants

#### Study population

Male patients undergoing rigid cystoscopy aged 20–75 years will be recruited from West China Hospital of Sichuan University. The trial will be ongoing from August 2015 to March 2016.

### Inclusion criteria

American Society of Anesthesiologists (ASA) Physical Status I–IIWithout history of urethral or prostatic surgeryWithout respiration or circulation disordersWithout chronic pain

### Exclusion criteria

Allergy to local anestheticsCoagulation disorder or usage of antiplatelet drugsInfection at the site of DPNB puncture pointSevere urethral stenosis

### Interventions

#### DPNB experimental group

For participants randomized to the DPNB group, a DPNB will be performed with a 22-G needle and 0.3 ml/kg of 0.33 % ropivacaine. After skin preparation and palpation of the arch of the lower border of the symphysis pubis, the base of the penis is gently pulled down and the needle is inserted on either side of the midline just distal to the inferior ramus of the pubic bone. The needle is advanced slowly, towards the center of the penile shaft, until loss of resistance is felt as it penetrates Scarpa’s fascia, where the local anesthetic is deposited equally on each side. All blocks will be performed by only one experienced attending anesthesiologist, who is good at the block procedure. Five minutes after DPNB, 10 ml of liquid glycerine will be instilled in the DPNB group at least 3 min before rigid cystoscopy.

#### Experimental group using combination of DPNB and tetracaine gel

In the DPNB and tetracaine gel combination group, a DPNB with 0.33 % ropivacaine (0.3 ml/kg) is performed as in the DPNB group. Five minutes after the DPNB, tetracaine gel is instilled, with a minimum dwell time of 3 min, before rigid cystoscopy.

#### Tetracaine gel control group

For men in the tetracaine gel group, DPNB is performed with saline. Five minutes after DPNB, tetracaine gel is instilled, with a minimum dwell time of 3 min, before rigid cystoscopy.

### Outcomes

#### Primary outcome

The primary outcome of this study is intensity of pain measured by a visual analog scale (VAS) at cystoscopic inspection of the external sphincter. VAS is an internationally recognized pain scale with 11 points, ranging from 0 (no pain) to 10 points (maximal pain). Pain can be rated as the following categories: no pain (0 points), mild pain (1–3 points), moderate pain (4–6 points), and severe pain (7–10 points). Participants will be well educated regarding the VAS once enrolled and asked to rate their pain level during the study.

#### Secondary outcomes

VAS scores, assessed prior to DPNB (baseline), at administration of lubricant, at cystoscopic inspection of the penile and bulbar urethra, the prostate and the bladder, and at withdrawal of the cystoscope, serve as secondary outcomes. Additionally, vital signs (heart rate, blood pressure, breath rate, and pulse oxygen saturation) are secondary outcomes that consider the discomfort and pain during the procedure and will be evaluated at the same time points as the VAS evaluation. Furthermore, the incidence of adverse events (penile hematoma, penile erection, autonomic movement and local anesthetic toxicosis) as secondary outcomes will also be recorded from the beginning of DPNB to the end of cystoscopy for evaluation of the safety of DPNB in rigid cystoscopy.

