### Data collection

Each participant’s characteristics such as age and body weight as well as ASA grade, durations of DPNB and rigid cystoscopy, VAS scores, vital signs, and the incidence of adverse events during rigid cystoscopy will be recorded in a designed data form by an investigator.

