### Sample size

The sample size calculation was based on the primary outcome, the intensity of pain measured on the VAS at cystoscopic inspection of the external sphincter. There are no data regarding VAS score for men when the rigid cystoscope passes through the membranous urethra. We therefore conducted a pilot study to determine the sample size prospectively. Based on our pilot data and literature relevant to pain during male rigid cystoscopy [11], assuming a standard deviation (SD) of 2.6, an α of 0.05, and a power of 90 %, 56 patients in each group are required to demonstrate a clinically relevant difference of 1.6 units in VAS score at cystoscopic inspection of the external sphincter.

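### Pre-block VAS and vital signs are classed as secondary outcomes, and the one-way ANOVA leaves these baseline values unused

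*Protocol article*

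**What the plan says.** The Primary outcome section names a single time point: "The primary outcome of this study is intensity of pain measured by a visual analog scale (VAS) at cystoscopic inspection of the external sphincter". The Secondary outcomes section lists the remaining VAS assessments, beginning with "VAS scores, assessed prior to DPNB (baseline), at administration of lubricant" and continuing through the later stages to withdrawal of the cystoscope, and gives the whole list secondary-outcome status. It then makes heart rate, blood pressure, breath rate and oxygen saturation secondary outcomes at the same time points, so their pre-block values are included.

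The Statistical analysis section has two branches. For the first, "Data with a normal distribution will be expressed as mean ± SD and tested by one-way ANOVA", with Dunnett's test as the follow-up. Continuous data that are not normal are "analyzed using the MIXED procedure of the SAS statistical program for repeated measures followed by Tukey-Kramer adjustments". Neither branch mentions a baseline covariate, and the second does not say what part the pre-block time point plays in the model.

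**The concern.** A score taken before the injection cannot be an effect of the injection. In a randomised comparison, any difference between arms at that point is due to chance. Such a score describes the sample and may explain variation in later scores, but it is not a result of treatment. Calling it an outcome has two possible consequences.

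- In the repeated-measures branch, the pre-block score is easily taken as one more response. A group effect averaged over time would then include a point at which the true effect is zero.
- In the ANOVA branch, a one-way model has group as its only term, so a baseline value already recorded for each man does no work.

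At stake are a clean list of outcomes, the meaning of any time-averaged group effect, and some precision, probably more for the vital signs than for the primary VAS.

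**Working it through.** **Inputs.** From the Sample size section: SD 2.6, difference 1.6, α 0.05, power 90%, 56 per group. From the Statistical analysis section: two-sided tests, and Dunnett's test after ANOVA. Three arms of 56 give 168 men and 168 − 3 = 165 residual degrees of freedom. The correlation R between baseline and outcome is not in the article. It is an assumption here, taken as 0.1 to 0.3.

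**1. The plan's own figure.** n = 2 × SD² × (1.960 + 1.282)² / difference² = 2 × 6.76 × 10.51 / 2.56 = 55.5, rounded up to 56. Power at 56 by the normal approximation is 90.3%. The stated size reproduces with no baseline adjustment, so it does not depend on this point.

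**2. Power of the named ANOVA branch, unadjusted.** The standard error of a difference is 2.6 × √(2/56) = 0.491, and the noncentrality is 1.6 / 0.491 = 3.256. The two-sided 5% Dunnett critical value for two comparisons with a control on 165 degrees of freedom is 2.232. Power per comparison from the noncentral t is 84.6%. The drop from about 90% comes from the Dunnett adjustment, which is a separate matter, and not from the missing covariate.

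**3. With a baseline covariate.** Residual SD = 2.6 × √(1 − R²).

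| Assumed R | Variance removed | Residual SD | Noncentrality | Power per Dunnett comparison |
|---|---|---|---|---|
| 0 | 0% | 2.600 | 3.256 | 84.6% |
| 0.1 | 1% | 2.587 | 3.273 | 85.0% |
| 0.2 | 4% | 2.547 | 3.323 | 86.1% |
| 0.3 | 9% | 2.480 | 3.414 | 88.0% |

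The covariate costs one degree of freedom (164 in place of 165), which does not change these figures.

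**4. Where R is likely to lie for the primary VAS.** The Inclusion criteria require men without chronic pain, and baseline is taken before both block and instrumentation. Scores near zero with little spread can predict little, which points to the top rows of the table. Heart rate and blood pressure do differ between men at rest, so a useful correlation with later values is more plausible for them. The article gives no figure for either.

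**5. Effect on a time-averaged group effect.** There are seven VAS time points: six in the secondary list, counting penile and bulbar urethra as one, plus the external sphincter. If all seven were equally weighted responses and the block lowered every post-block score by 1.6, the averaged effect would be 1.6 × 6/7 = 1.37, one seventh too small. This applies only to an effect averaged over all times. A contrast at the sphincter alone, from a model with group-by-time terms, is not diluted.

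**The case against.** The strongest reply is that this is a labelling slip in a condensed article. An unadjusted comparison is valid under 1:1:1 randomisation, and covariates are commonly settled in an analysis plan that is not shown. The abstract describes the secondary VAS outcomes as those at other time points and gives the assessment schedule separately, so the Secondary outcomes section may simply have merged the two. A longitudinal model that keeps baseline as a response and constrains the arms to a common mean is also a recognised alternative to ANCOVA.

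Much of this stands, and it rules out several stronger readings that a reader might infer:

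- **That the plan specifies a between-arm test of baseline VAS.** It does not. Such a test could only be inferred from the outcome label and the general analysis paragraph.
- **That the primary analysis is invalid or forgoes a sizeable gain.** The comparison is valid, and no stated correlation supports a large gain.
- **That one-way ANOVA is the only primary analysis.** It is the branch for normal data. Otherwise the MIXED branch applies, and the power figures above do not cover it.
- **That age should also be a covariate.** Data collection lists it among "characteristics such as age and body weight as well as ASA grade", but nothing in the article links it to pain.
- **That the MIXED model necessarily dilutes the effect.** Its terms are not given.

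The reply does not remove the outcome label, which is on the page. Nor is the group-only model merely an absent detail: the article names a one-way ANOVA, and a better use of data already collected is available.

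**Conclusion.** The point holds in a limited form, with minor severity. Pre-block VAS and pre-block vital signs are wrongly classed as outcomes, and the ANOVA named for normal data does not use them. The validity of the primary comparison and the 56 per group are unaffected.

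For the primary VAS, adjustment takes power per Dunnett comparison from 84.6% to between 85.0% and 88.0%, a gain of 0.4 to 3.4 percentage points. That rests on an assumed R of 0.1 to 0.3 and on the article's SD of 2.6 and difference of 1.6. If nearly all men score zero before the block, the gain is close to nil. A benefit for heart rate and blood pressure is more plausible but cannot be sized from the article.

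**What to change.** 1. In Secondary outcomes, restrict the VAS and vital-sign outcomes to post-block time points, and report the pre-block values with the baseline characteristics.
2. In Statistical analysis, replace the one-way ANOVA for each post-block VAS score and vital sign by an ANCOVA with arm and that measure's own baseline value. Keep the Dunnett contrasts against the tetracaine gel control.
3. In the MIXED model, state that baseline is a covariate and that the responses are the post-block time points only, so that no group effect averaged over time includes the pre-block point.

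Age need not be added. The cost is a few sentences of wording, since the baseline values are already scheduled for collection and the sample size does not change.
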